#### Sampling strategy

In this study stratified random sampling technique will be used for selection of participants where stratification will be done based on environmental factors that are likely to affect exposure. Since both distance from fixed contamination source as well as local environment features such as meteorology, topography, etc. are the major factors affecting the dispersion of both ambient air as well as water pollutants [26], a map of the study area was created to assist in selection of exposure monitoring locations and in participant sampling (see Fig 3). Briefly, taking Birlagram industrial region as the centre, villages located within consecutive circles of radius 2 kilometres (km), 5km and 10km were demarcated on the map using ArcInfo (version 10). This strategy was used as it is expected that gaseous pollutants’ dispersion occurs homogenously in all directions independent of anthropogenic roadways and that with increase in distance the pollutant concentration will become diluted enough to prevent adverse health effects [27]. Based on seasonal wind pattern data retrieved from local authorities, the north-eastern quadrant of the circular study area was seen to be the downwind area for most of the year. The downstream direction of River Chambal falls in the north-western quadrant of the circular study area. Therefore the majority of the pollutants are expected to disperse in the northern direction increasing the potential risk faced by the residents and so, we decided to over-represent the northern hemisphere.

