**Fig 3 pone.0264154.g003:**
[figure not shown]
Map of the study area created by research team to assist in selection of exposure monitoring locations and in participant sampling. [Note: The inset in the map shows the Ujjain district of the central Indian province of MP. Within the Khachrod Tehsil of the Ujjain district, lies the study area of the current project. Considering the Birlagram industrial region as the centre, three concentric circular regions were demarcated based on distance (2, 5 and 10 km from the centre)].

Finally, 2000 participants will be selected from the villages in the northern hemisphere while 1003 will be taken from the villages in the southern hemisphere within the 10km radius comprising a total of 3003 participants. In each hemisphere, a fixed number of villages will be selected randomly from those situated in each of the 0-2km, 2-5km and 5-10km zones. Further in each selected village, using the list of all individuals residing in the villages that will be retrieved from the local authorities as the sampling frame, individuals meeting the eligibility criteria will be randomly invited for participation in the study. Total number of individuals sampled in each village will be proportionate to the total population of the selected village.

Participants will be selected for the study only if they fulfill all the following criteria:

Adults (≥18 years of age) of both genders (except pregnant women),Should have been residing for at least one year in the selected village,No history of neuropsychiatric conditions that might hinder completion of neurobehavioral tests,No history of other conditions that are contraindications for performing Pulmonary function test (PFT) like presence of any active disease (e.g. pulmonary Tuberculosis, active haemoptysis, orofacial pain, acute respiratory infection including COVID-19 i.e. coronavirus disease caused by SARS-Cov-2 virus) or recent history (within previous 1 month) of myocardial infarction/aneurysm/surgery, etc.

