Finger tapping test (FTT)	Motor functioning, specifically, motor speed and lateralized coordination	We will use a shorter version of Finger tapping test [55]. In this test, the subject’s palm of dominant hand should be immobile and flat on the board, with fingers extended, and the index finder placed on the counting device. The subject taps his index finger on the lever as quickly as possible within a 10 seconds time interval, in order to increase the number on the counting device with each tap. Such five trials are performed with 10 seconds rest interval in-between each trial [55].	The score is the mean score of trials 3–5.

*v) Clinical investigations (PFT and ECG)*. PFT will be conducted using portable spirometer (Cosmed**®** Pony FX) on comfortably seated participants by a trained technician, supervised by a trained physician, following national guidelines [56], to measure forced expiratory volume in first second (FEV_1_), forced vital capacity(FVC), and peak expiratory flow. Of three acceptable spirograms defined as the difference between the two largest FVC and the two largest FEV_1_ measurements are less than or equal to 0.150 litres, the best value for each parameter will be included for analysis. The predicted values for the FVC will be calculated for each subject using Kamat’s Regression equation [57]. For categorizing pulmonary function impairment, cut-off of 80% of predictive FVC and 70% of FEV_1_/FVC ratio will be taken [58].

A portable 12-lead Electrocardiogram device (BPL CardiArt**®** 9108D) will be used to measure electrical activity of the heart following American Heart Association guidelines [59]. Briefly, in a private screened area, ECG recording will be done by previously trained medical staff on the chest and limbs of supine and relaxed participants. Trained physicians will interpret the ECG recording as per standard guidelines [60].

*vi) Laboratory investigations*. A battery of clinical laboratory investigations comprising of Random Blood Glucose, Complete Blood Counts, and Lipid profile (Total cholesterol, High and low density lipoprotein cholesterol, and Triglyceride) will be carried out for all participants of the study. Blood sample collection will be carried out by trained technician according to standard operating procedure in compliance with WHO Best Practices [61].

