#### Data management and analysis

All participants’ data will be coded by assigning unique identifiers. These codes will be used to identify and link various parameters of the individual participants. Data from the filled questionnaires/clinical proforma as well as the laboratory analysis values will be entered into the latest version of Microsoft Excel spreadsheets. Statistician of the team will supervise data entry and to ensure error-free data at least 10% of the entered data will be randomly verified.

Once data entry is complete, hard copies of questionnaire/proforma will be stored in a secure archive in the institute. Similarly, all entered data will be stored in password protected computer systems with access restricted to the research team alone. The data collected/generated in this study will be stored for a period of ten years. The primary investigator will be in-charge of data safety and back-up maintenance. Anonymized data set will be shared publicly during publication of study results.

All statistical analyses will be performed using IBM SPSS Statistics (version 25). For ordinal and continuous variables, the values will be given as descriptive statistics (like mean, median, standard deviation, 95% confidence interval, interquartile range); and categorical variables will be given as numbers (percentages) and proportions. Association for different health aspects with pollution level of various parameters of air/water will be made using Pearson’s chi-square test for independent categorical data. By considering the variability within and between groups; t-test and ANOVA will be used to analyze the mean differences between two and more groups respectively for various anthropological parameters, the concentration of air/water pollutants, etc. The Mann–Whitney U test and Wilcoxon signed ranks test will be used for independent and dependent for ordinal and continuous data with respect to different health aspects. Pearson and Spearman’s correlation coefficient will be used to examine the association between different variables. Multiple linear and logistic regression models will be used to estimate the relationship for different neurological assessments with a set of the independent variable. For all statistical tests, two-sided P-values <0.05 will be considered to be significant.

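### A raw 70% FEV1/FVC cut-off in adults of every age, tested against pollution level by an unadjusted chi-square test, lets age differences between zones pass as a lung effect

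*Protocol article*

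**What the plan says.** All references are to the protocol article.

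- **Impairment label** (Health assessment, clinical investigations): "For categorizing pulmonary function impairment, cut-off of 80% of predictive FVC and 70% of FEV_1_/FVC ratio will be taken".
- **Prediction** (same paragraph): "The predicted values for the FVC will be calculated for each subject using Kamat’s Regression equation". No predicted value is mentioned for the ratio, and the equation's residual SD is not given.
- **Who is measured** (eligibility list under Sampling strategy): "Adults (≥18 years of age) of both genders (except pregnant women". There is no upper age limit.
- **How the sample is balanced** (Sampling strategy): "stratification will be done based on environmental factors that are likely to affect exposure". The factors described are distance and direction; age and sex are not among them.
- **Test for categorical outcomes** (Data management and analysis): "Association for different health aspects with pollution level of various parameters of air/water will be made using Pearson’s chi-square test for independent categorical data".
- **Where regression is planned** (same section): "Multiple linear and logistic regression models will be used to estimate the relationship for different neurological assessments with a set of the independent variable".

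The Discussion says that data on several confounders will be collected and admits that residual confounding may remain. It does not link those data to a lung-function model.

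**The concern.** A fixed threshold on a quantity that drifts with age in healthy people has a false-positive rate that drifts with age too. The raw ratio is open to this directly, because nothing in the label takes age into account.

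Two things follow. First, the reported prevalence of impairment mixes normal ageing with disease, to a degree that the documents do not let one judge. Second, the fourth study objective is to link exposure with health effects. Random selection within villages reproduces each village's age structure but does not equalise age between zones or hemispheres. If those structures differ, an unadjusted chi-square test compares ages as well as exposures.

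**Working it through.** **The plan's own figures.** The article gives no rate of false labelling, so there is none to reproduce. Its only computed figure, the sample size, does reproduce: 1.96² × 0.26 × 0.74 × 1.3 × 1.25 / 0.02² = 3002.7, rounded up to 3003. It is based on ECG abnormality and does not bear on this point.

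**Inputs.** From the article: the two cut-offs, ages 18 and over, 2000 northern and 1003 southern participants, two-sided 0.05. Assumed, because the article gives none: the healthy mean ratio at age 20, its yearly fall, its SD, the residual SD of FVC, and the age distributions.

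**Step 1: ratio below 0.70 by age.** Healthy share labelled = Φ((0.70 − mean at that age) / SD), with mean at that age = mean at 20 − fall × (age − 20). Example with mean 0.87, fall 0.002, SD 0.06:
- age 20: Φ(−0.17/0.06) = 0.23%
- age 60: mean 0.79, Φ(−0.09/0.06) = 6.68%, a 29-fold rise

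| Mean at 20 | Fall per year | SD | Age 20 | Age 60 | 60 v 20 |
|---|---|---|---|---|---|
| 0.86 | 0.001 | 0.05 | 0.07% | 0.82% | 11.9-fold |
| 0.86 | 0.0015 | 0.07 | 1.11% | 7.66% | 6.9-fold |
| 0.87 | 0.002 | 0.06 | 0.23% | 6.68% | 29.0-fold |
| 0.86 | 0.002 | 0.06 | 0.38% | 9.12% | 23.8-fold |
| 0.88 | 0.0025 | 0.06 | 0.13% | 9.12% | 67.6-fold |
| 0.86 | 0.0005 | 0.06 | 0.38% | 0.98% | 2.6-fold |
| 0.84 | 0 | 0.06 | 0.98% | 0.98% | 1-fold |

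**Step 2: what an age gap does to an unadjusted comparison.** Ages are normal with SD 14, limited to 18–85. Mean age is 38 in the group of 1003 and 38 + d in the group of 2000, with no exposure effect. The last column is the normal-approximation chance of p<0.05 with the older group looking worse; with equal ages it would be 2.5%.

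| Scenario (mean at 20, fall, SD) | d | Shares labelled | Chance |
|---|---|---|---|
| 0.86, 0.001, 0.05 | 2 | 0.31% v 0.35% | 3.4% |
| | 5 | 0.31% v 0.42% | 5.4% |
| | 10 | 0.31% v 0.55% | 12% |
| 0.87, 0.002, 0.06 | 2 | 2.15% v 2.47% | 7.5% |
| | 5 | 2.15% v 3.04% | 28% |
| | 10 | 2.15% v 4.22% | 85% |
| 0.88, 0.0025, 0.06 | 2 | 2.59% v 3.05% | 10% |
| | 5 | 2.59% v 3.87% | 44% |
| | 10 | 2.59% v 5.61% | 98% |

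Counting significant results in both directions raises the smallest 5-year figure to about 6% and leaves the largest at 44%. North against south is used here only because the article gives those group sizes. With equal age mix, or with no fall in the ratio, there is no spurious difference.

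**Step 3: FVC below 80% of predicted.**
- Residual SD constant in litres: Φ(−0.20 × predicted / SD). From predicted 4.0 L to 2.0 L the share goes from 0.4% to 9.1% (SD 0.3 L), 2.3% to 15.9% (0.4 L) or 5.5% to 21.2% (0.5 L).
- Residual SD proportional to predicted (CV 11 to 15%): Φ(−0.20 / CV), which is 3.4 to 9.1% depending on the CV and the same at every predicted value.

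The article does not say which case applies.

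**The case against.** The strongest reply has four parts.

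- **The numbers are assumed.** The slopes, SDs and age gaps are not in the article. This stands. The size can be given only as a range, and the range includes no effect.
- **FVC is already individually referenced.** This also stands. A reader might infer that both cut-offs mislabel women, short people and older people many-fold. For FVC that needs a residual SD that is not proportional to the predicted value, which nothing shown establishes.
- **Adjustment would remove the confounding.** A model with age, sex and height would deal with the spurious zone difference without changing the cut-off, and an analysis plan that is not shown might contain one. It is therefore wrong to call the spurious exposure effect independent of how the test is done: it needs both an unequal mix and an unadjusted analysis. But the article states the test for categorical health outcomes and names regression only for neurological ones. As written, it steers the lung categories to the unadjusted test.
- **The cut-offs have a cited source, and the dichotomy may not be the only lung outcome.** The best spirometry values are also kept for analysis, and mean comparisons and correlations are planned for continuous data. This supports keeping the fixed cut-offs for comparability and weakens any claim that early loss in young adults will be missed. It does not supply the missing age adjustment.

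A reader might also infer that the reported prevalence is largely an age and sex effect, or set the possible bias against the plan's 2% margin of error. Neither is supported. The article gives no true prevalence and no age or sex distribution, and that margin is the precision for estimating ECG abnormality.

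**Conclusion.** The point holds for the raw FEV1/FVC cut-off combined with the unadjusted chi-square test. If the healthy ratio falls with age, the label's false-positive rate rises with age and zone comparisons are open to confounding by age.

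The size is unknown from the documents. For falls of 0.001 to 0.0025 per year, the age-60 to age-20 multiple is about 7 to 68, and a 5-year gap in mean age gives roughly a 5 to 44% chance of a significant result with no exposure effect. A 2-year gap has little effect, and with a small or nil fall the problem shrinks or disappears. These chances assume independent observations, a normal ratio at each age and the age distributions stated in the working.

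For FVC the concern is conditional on the unknown residual SD. Nothing here judges the cut-offs as clinical rules; the issue is their use as an outcome in an exposure comparison.

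**What to change.** In Data management and analysis, state that the exposure analysis of lung function will do one of the following, with age, sex and height as covariates:
- analyse FVC and FEV1/FVC as continuous outcomes by linear regression (preferred, since it avoids the threshold), or
- analyse the impairment categories by logistic regression.

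Where the prediction source or another external reference supplies residual SDs and a ratio equation, also report impairment by the 5th-percentile lower limit of normal. That holds the healthy share labelled at 5% per index in every subgroup, provided the reference fits this population. Keep the fixed 80% and 70% cut-offs as a reported definition, for comparability with other surveys.

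Do not derive normal limits from the 5–10 km residents. They are part of the exposure gradient under study, so calibrating normality on them could hide a real effect.

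Cost: a little more analysis work and two prevalence figures to report instead of one. No new measurement is needed: height is measured and demographic details are collected by questionnaire.

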#### Environmental monitoring of pollutants at study sites

Pollutants for assessment in both environmental and human matrices were selected based upon their relevance to viscose rayon and associated chemical manufacturing industry identified through review of previously published literature [9].

*i) Monitoring of gaseous pollutants in ambient air*. The ambient air monitoring will be carried out in the study area (see Fig 2) for identified gaseous pollutants viz., CS_2_, H_2_S, HCl, Cl_2_, and SO_2_ using a factory calibrated, electrochemical sensor based multi-gas monitor (Make: Swan**®** Environmental Pvt. Ltd. India, Model: GRI-IAT; Sensor make: Membrapor**®**, Switzerland). The monitoring will be carried out in post-monsoon season (October-January). The instrument has an inbuilt geographical positioning system to record the coordinates of sampling site. The ambient air monitoring will be carried out continuously for 24 hours in at identified sites. In case of cluster of sites, a representative site will be identified for gaseous monitoring. The monitor will be placed at more than 3 metres height from ground level at a place having uninterrupted power supply. The data loggers present in the instrument will store the data at set frequency and will be utilized for further statistical analysis. The sampling and monitoring of ambient air for said pollutants will be carried out following the existing guidelines of CPCB, Ministry of Environment, Forests and Climate Change, New Delhi, India [28].

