To undertake the afore-mentioned three tests, briefly, a total of 5 mL sample of venous blood will be collected from the median cubital vein of the participants by trained technician maintaining sterile precautions. 2 mL blood will be collected in ethylene diamine tetra acetic acid vacutainer for complete blood count which will be processed within 4 hours using a fully automated hematology analyzer (Sysmex**®**). 3 mL blood sample will be collected in plain vacutainer from which serum will be separated and stored at -20°C till analysis. The serum will be used for estimation of lipid profile using semi-automated biochemistry analyzer (ERBA**®**). Random blood glucose will be estimated on the spot from a drop of blood at the time of sample collection, using a hand held glucometer (Accu-Chek**®**).

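### Triglyceride and random glucose come from one draw not tied to meals, so if meal timing differs between villages it can pass for a pollution effect in the unadjusted tests

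*Protocol article*

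**What the plan says.** Under Health assessment, item vi (Laboratory investigations), everyone has a random glucose, a blood count and a lipid panel: "Lipid profile (Total cholesterol, High and low density lipoprotein cholesterol, and Triglyceride) will be carried out for all participants of the study". One collection serves all three: "To undertake the afore-mentioned three tests, briefly, a total of 5 mL sample of venous blood will be collected". The 3 mL plain tube gives the serum for the lipids: "The serum will be used for estimation of lipid profile using semi-automated biochemistry analyzer". On glucose the article states: "Random blood glucose will be estimated on the spot from a drop of blood at the time of sample collection". No fasting condition, fixed hour of draw or record of time since eating is stated.

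Exposure is a property of place. Under Sampling strategy, "a fixed number of villages will be selected randomly from those situated in each of the 0-2km, 2-5km and 5-10km zones" in each hemisphere. Under Environmental monitoring, gases are measured at sites ("In case of cluster of sites, a representative site will be identified for gaseous monitoring") and groundwater is sampled in selected villages.

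Under Data management and analysis, health outcomes are related to pollution level by chi-square. The t-test, ANOVA, Mann-Whitney and Wilcoxon tests and correlation coefficients are also listed. Multiple linear and logistic regression is named for neurological assessments only.

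**The concern.** Triglyceride and glucose depend on how recently a person has eaten. If one village is seen mainly in the morning and another mainly after midday, mean values can differ for that reason alone. Villages and sites also carry the exposure values, so such a difference would run along the same axis as pollution. Random selection of people within a village does not remove a difference between villages, and an unadjusted test cannot separate the two causes.

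Lipids matter here. The Discussion lists the lipid profile among the documented effects of carbon disulphide, and the last objective in the Introduction is the association between exposure and health effects. The Discussion also says that the study takes place amid a dispute between residents, manufacturers and authorities, so a false association would have consequences.

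**Working it through.** **The plan's own figure.** The only computed figure is the sample size, set by the proportion with ECG abnormalities: 1.96² × 0.26 × 0.74 × 1.30 × 1.25 / 0.02² = 3002.69, rounded up to 3003. It reproduces and is not affected by this point.

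**What follows from the text.**
1. Glucose is random and is read at the time of collection.
2. The lipid serum comes from that same collection, so triglyceride has no fixed relation to meals.
3. Exposure varies by village or site.
4. The tests named for these outcomes have no covariates.

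Meal timing is therefore uncontrolled at the draw and unadjusted in the stated analysis. Whether it differs between villages is not stated.

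**Conditional illustration.** The document gives no triglyceride SD, meal effect or fed share. The values below are assumptions, and they show only how the result depends on the gap in fed share. The one input from the document is the pair of group sizes: "2000 participants will be selected from the villages in the northern hemisphere while 1003 will be taken from the villages in the southern hemisphere". North against south is used for convenience and is not the lipid comparison that the plan states. Village clustering is ignored.

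- False difference in SD units: δ = (meal shift in SD) × (difference in fed share).
- SE = √(1/2000 + 1/1003) = 0.0387 SD.
- Chance of two-sided P < 0.05 with no pollution effect: Φ(δ/SE − 1.96) + Φ(−δ/SE − 1.96).

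| Meal shift (SD) | Gap in fed share | δ | Chance of P < 0.05 |
|---|---|---|---|
| any | 0 | 0 | 5% |
| 0.2 | 10 points | 0.02 | 8% |
| 0.3 | 20 points | 0.06 | 34% |
| 0.5 | 30 points | 0.15 | 97% |

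The result runs from the nominal level to near certainty according to a gap that nobody can read from the document. The table is not an estimate for this study.

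**Loss of precision when the fed share is equal.** With half the participants recently fed, the added variance is (shift/2)². Assume a rise of 45 mg/dL and an SD of 60: (22.5)² = 506, and √(3600 + 506) = 64.1, so the SD rises by about 7%. Assume 15 mg/dL and an SD of 90: (7.5)² = 56, and √(8100 + 56) = 90.3, a rise of 0.3%. If the assumed SD already mixes meal states, nothing is added.

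**The case against.** The strongest objection is that this is mostly a detail left out of a condensed article. The questionnaire, the clinical proforma and the blood-collection operating procedure are not shown, and any of them might ask about the last meal or stamp the time. The Discussion also promises data on diet and lifestyle confounders. This stands in part: absence of a form item from the article does not show that it is absent from the study. It does not dispose of the point. The single collection and the random glucose are stated, not omitted, and the named analysis gives these outcomes no adjustment even if the times are recorded. Habitual diet is not the same as hours since the last meal.

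The second objection stands in full: nothing in the article gives clinic hours, visit order or place of examination, so an imbalance by village is a possibility only. Each hemisphere also pools villages from three distance zones, so ordinary differences in clinic hour would partly average out.

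Non-fasting sampling is in itself a workable choice for a field survey of about 3000 people, and the point does not ask for it to change.

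A reader might go further and infer that the whole lipid profile is compromised, that the planned tests will produce false pollution effects, or that meal-related noise will hide a real one. The article supports none of these. Total and HDL cholesterol are much less affected, the method for LDL is not stated, no imbalance is shown, and the added noise is at most about 7% of the SD under the assumptions above.

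**Conclusion.** The concern holds in a narrow form. It covers triglyceride and random glucose, and LDL only if that is calculated from triglyceride. For these outcomes the stated design leaves meal timing free at the draw, ties exposure to place and names only unadjusted tests, so a difference between villages in hour of draw or fed share could be read as an effect of pollution. The size of any such bias cannot be derived from the document; with no gap in fed share there is no bias and a small loss of precision. Lipids and glucose do not set the sample size and are among many outcomes. The point is minor, but worth settling before fieldwork because time since eating cannot be reliably recovered afterwards.

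**What to change.** 1. Record the clock time of the draw and the hours since last food for each participant. If the proforma already holds these items, say so in the protocol.
2. Spread morning and afternoon sessions across the distance zones in both hemispheres, so that clinic hour does not run with exposure. Adjustment alone is weak if a village is seen at only one time of day.
3. Analyse triglyceride and random glucose against pollution level in a regression with hours since last meal and hour of draw as covariates, and extend the regression sentence under Data management and analysis to cover them.
4. Report non-HDL cholesterol (total minus HDL, both already measured) alongside triglyceride, as a measure less sensitive to meals. No ranking of the lipid outcomes is needed.
5. State whether LDL is measured directly or calculated.

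The cost is one question, one time stamp and slight scheduling effort. No extra blood, visit or participant is required.
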